**Study endpoint and outcome measures**

**Primary endpoints:**

28 day mortality and safety of TPE

**Secondary endpoints:**

Improvement of organ function as evaluated per SOFA score

Changes in laboratory inflammation markers

ICU length of stay

Number of days on mechanical ventilation

**Randomization** Eligible consented patients will be randomized after their stratification by ICU center and two PaO2/FIO2 ratio categories (> 150 and ≤ 150). Randomization will occur in variable block sizes of 4 to 8 patients. We will utilize a web-based randomization service, [randomize.net](http://randomize.net/) to allocate patients to their respective strata prior to the intervention or control therapy. Given the nature of the TPE technology, the intervention will be unblinded (open label); hence, no enrollment concealment will be expedited. However, the lack of allocation concealment will be mitigated as much as possible by the following measures. First, the primary outcome of mortality will not be disputable. Second, we have standardized co-interventions that impact on mortality as much as possible. These interventions include a) concomitant drug therapies for COVID-19, b) algorithms for mechanical ventilation including the early use of prone-ventilation, low tidal volume ventilation and neuromuscular blockade, c) the standard use of a broad spectrum antibiotic(s) for a minimum of 7 days to treat any potential superinfection be a bacterial pneumonia and d) standard criteria to initiate intermittent hemodialysis or CRRT such as hyperkalemia, profound metabolic acidosis, oliguria unresponsive to furosemide challenges of 1-1.5 mg/kg, e) the presence or development of coagulopathy defined as INR > 3.0 or Fibrinogen < 1.0 will be treated in a standard fashion in both the intervention and control group. We will define the date/time of appropriateness for ICU transfer irrespective of treatment allocation and recognizing that some COVID-19 patients randomized to the intervention group may improve to the point of appropriateness to transfer to the medical ward but requiring ICU care only to deliver remaining TPE doses as outlined in the protocol.

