The concept of the suggested protocol was derived from our own preliminary clinical observations. In brief, therapeutic plasma exchange (TPE) has the potential to be a rescue therapy in intubated ICU patients with fulminant COVID-19. This is because patients may present with ARDS, septic shock and/or MSOF and TPE has been used in severe sepsis, MSOF and fulminant SARS-CoV. Recently, the US and European Food and Drug Administration (FDA) has extended the use of TPE to include serious COVID-19 cases. The rationale is that TPE can remove interleukins-3, 6, 8, 10, interferon-gamma and tumor necrosis factor-alpha. Thus, it may reduce the cytokine storm and cascade associated with fulminant COVID-19 disease. In that sense, TPE can be a safe, easy and less complex alternative rescue therapy, especially when compared to other rescues treatment such as convalescent plasma transfusions, which requires the utilization of more resources and specialized equipment. [9-25]

In the Kingdom of Saudi Arabia, there are currently more than 60.000 COVID-19 cases and the death toll is increasing. This has led to the need for ICU care, despite the Kingdom’s prompt actions to apply lockdowns and curfew orders early on. COVID-19 is highly transmittable and is threatening our global health, economy and way of life. Accordingly, the development of effective therapeutic strategies to manage patients who have COVID-19 that is severe enough to requiring hospitalization, supplemental oxygen therapy and/or ICU admission is a research priority.

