**Serious COVID-19 is defined as:**

Dyspnea

Altered level of consciousness

Respiratory frequency ≥ 30/min

Blood oxygen saturation ≤ 93% (despite oxygen therapy via nasal cannula 10L/min)

Partial pressure of arterial oxygen to fraction of inspired oxygen ratio < 300 (P/F ratio<300), and/or development of bilateral pulmonary infiltrates within 24 to 48 hours. [4-8]

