**Statistical analysis**

Continuous data will be summarized as mean ± standard deviation, and compared among groups with student t test or Wilxocon’s rank sum test as appropriate. Discrete data will be summarized as number (%) and compared by chi square or Fisher’s exact test as appropriate. All statistical tests are two tailed, considered significant with p value < 0.05 Survival analysis will be visually presented by Kaplan Meier’s Curve, and compared by hazard ratio. Statistical software SPSS 24.0 will be used.

Crude 30 and 90-days survival distributions between treatment [TPE] and control [no TPE] groups will be described using proportions and Kaplan Meier distributions. Crude differences will be tested using Chi Square test [for proportions] and a log-rank test [for the Kaplan Meier survival distributions]. A multivariable analysis of the primary 30 and 90-days survival outcome will be conducted using a Cox Proportional Hazard model where the main effect of treatment [TPE versus no TPE] and relevant confounding variables: age, gender, admission PaO2/FIO2 ratio, admission APACHE II and SOFA scores, presence of acquired coagulopathy and high vs low CRS group (already defined in previous paragraphs) will be entered into the model a-priori.

Similarly, a logistic regression multivariable model including the aforementioned variables will be fit to determine the independent effect of the TPE treatment on the binary outcome of 30 and 90 days survival.

Daily whole blood and effluent plasma samples will be obtained and assayed for various inflammatory markers IL-6, C-RP, ferritin etc. General estimating equations using random effects models will be used to describe the temporal changes in whole blood [in both treatment and control groups] and effluent plasma [in TPE group only]. Standard comparisons of the change in inflammatory markers using robust variance estimators will be used to compare the changes in these markers between treatment and control group.

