**Data collection**

Clinical information of all enrolled cases will be retrieved from the hospital electronic/paper records system, including the: baseline demographic data, days of illness duration, presenting symptoms, radiological findings (CXR and Chest CT scans when possible), Sequential Organ Function Assessment (SOFA) and APACHE II scores. Data will be collected upon hospital/ICU admission, and prior to the first TPE session (Day 0) then on days 3, 7, 14, 30 accordingly and/or upon ICU/hospital discharge. Laboratory infectious marker testing results like culture from respiratory, urinary or blood culture will be collected accordingly.

Common laboratory and inflammatory markers (see below) will be collected on a daily basis:

1. CBC differential to include percent and absolute lymphocyte count and percent and absolute neutrophil count

2. Chemistry panel to include Total protein, Albumin, Lactate Dehydrogenase (LDH), Aminotransferases (ALT, AST), Procalcitonin

3. Cardiac biomarkers (e.g. cardiac troponins)

4. CK

5. Ferritin, LDH

6. Full coagulation profile to include PT, APTT, fibrinogen and D-dimer levels

7. C Reactive Protein (CRP) and erythrocyte sedimentation rate (ESR)

8. Interleukin-6

RT-PCR test for SARS-CoV-2 will be done and will be monitored during treatment and at day 14 of recovery or discharge, whatever is later. Also, we will be monitoring: mechanical ventilation (MV) and modes, intranasal oxygen inhalation, non-invasive mechanical ventilation, number of days of MV or nasal oxygen support, medication regimens (i.e., hydroxychloroquine, anti-viral therapies, steroids, tocilizumab, etc.), complications (including acute renal failure, acute coronary syndrome, myocarditis, acute respiratory distress syndrome, GI complications, CNS complications and nosocomial infections).

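### Ventilator days are compared by an unadjusted test that ignores recorded ventilation state at entry, which costs some power and could be avoided at no cost

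*Protocol*

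**What the plan says.** - **Endpoint.** Protocol, Secondary endpoints, lists "Number of days on mechanical ventilation" with no starting point, time window or rule for deaths.
- **Test.** Protocol, Statistical analysis, has continuous data "compared among groups with student t test or Wilxocon’s rank sum test as appropriate", and adds: "All statistical tests are two tailed, considered significant with p value < 0.05". No other analysis is named that covers ventilator days.
- **Covariates.** The adjusted Cox and logistic models are for survival only. Their list begins "age, gender, admission PaO2/FIO2 ratio, admission APACHE II and SOFA scores" and goes on to coagulopathy and CRS group. Ventilation state is not on it.
- **Stratification.** Protocol, Randomization, uses ICU center and a PaO2/FIO2 cut at 150.
- **Who can enter.** The Introduction says that TPE "has the potential to be a rescue therapy in intubated ICU patients with fulminant COVID-19". The definition of serious disease includes "Blood oxygen saturation ≤ 93% (despite oxygen therapy via nasal cannula 10L/min"). No criterion requires or excludes ventilation.
- **What is recorded.** Protocol, Data collection, lists "mechanical ventilation (MV) and modes, intranasal oxygen inhalation, non-invasive mechanical ventilation" and the days on support. Response assessment adds daily ventilator requirement and mode.

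**The concern.** A patient intubated at randomisation starts with the endpoint already running. A patient on nasal oxygen may finish with zero ventilator days. If both kinds enter in numbers, much of the spread in ventilator days reflects the state at entry, which treatment cannot change. An unadjusted comparison leaves that spread in the error term, and a chance imbalance in entry state goes straight into the estimate.

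What is at stake is precision on a named secondary endpoint. The trial is also meant to inform a definitive trial's sample size, and a spread that mixes two entry states is a poor input for that.

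**Working it through.** The protocol states no power, standard deviation, effect or ventilated share for this endpoint, so there is no figure to reproduce. From the documents come about 60 per arm, two-sided 0.05 and expected mortality of 50%. Everything else below is assumed.

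**1. Analytic check.** Let *f* be the share ventilated at entry and *g* the gap in mean days between the two states, in within-state SDs. The share of variance explained by entry state is R² = f(1−f)g² / (1 + f(1−f)g²). Fix the effect so that the adjusted analysis has 80% power. The unadjusted power is then about Φ(2.80·√(1−R²) − 1.96).

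Example, f = 0.5 and g = 1: R² = 0.25/1.25 = 0.20, and Φ(2.80 × 0.894 − 1.96) = Φ(0.55) ≈ 71%. The adjusted analysis would need 60 × (1 − 0.20) = 48 per arm for the power that the unadjusted one has with 60.

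| f | g | R² | unadjusted power (adjusted = 80%) |
|---|---|---|---|
| 0.5 | 0.5 | 0.06 | 78% |
| 0.5 | 1 | 0.20 | 71% |
| 0.5 | 1.5 | 0.36 | 61% |
| 0.5 | 2 | 0.50 | 51% |
| 0.9 | 0.5 | 0.02 | 79% |
| 0.9 | 1 | 0.08 | 77% |
| 0.9 | 2 | 0.27 | 67% |

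**2. Simulation, plain rank-sum against van Elteren.** The stratified statistic is Z = Σ[(W_s − E W_s)/(N_s+1)] / √Σ[Var(W_s)/(N_s+1)²], summed over the two entry states. Assumed: median 12 days if ventilated at entry; otherwise 40% later intubated, median 9 days; log SD 0.7; cap at 28 days. TPE shortens days by 30% and lowers later intubation to 30%. In the deaths version, mortality is 65% if ventilated at entry and 35% if not (average 50% when f = 0.5), 10 points lower on TPE, and deaths take the worst rank.

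| Ventilated at entry | No deaths: plain vs stratified | Gain | Deaths ranked worst: plain vs stratified | Gain |
|---|---|---|---|---|
| 30% | 32% vs 47% | 15 | 29% vs 35% | 6 |
| 50% | 38% vs 57% | 19 | 29% vs 36% | 7 |
| 70% | 51% vs 67% | 16 | 31% vs 37% | 6 |
| 90% | 67% vs 73% | 6 | 31% vs 33% | 2 |

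Repeat runs with deaths ranked worst, for 30% to 70% ventilated, gave 28–32% against 35–38%, a gain of about 4 to 9 points. Null rejection was about 5% for both tests. In the 50% case without deaths, entry state explains about 30% of the variance.

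**3. A second set of assumptions.** Here 20% to 70% of those not ventilated at entry are later ventilated, the mean duration is 12 days, mortality is 60% if ever ventilated and 15% otherwise, and treatment multiplies duration and later ventilation by 0.65. In the six settings with total mortality of about 46% to 56%, the gain was about 3 to 24 points for the rank tests and 3 to 15 points for covariance analysis over the t test. With 90% ventilated at entry it was about 2 to 8 points. If treatment only prevents intubation, the gain was at most about 3 points and power was at most 37% either way.

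**4. Chance imbalance.** With half ventilated and no balancing, the normal approximation to the chance of a difference above 10 points is 2(1 − Φ(0.10/√(2 × 0.25/60))) = 27%. The exact binomial value (7 or more patients out of 60) is 23.5%. If P/F stratification balances part of it, with ventilation at 75% and 25% in two equal strata, the chance is about 17%; at 85% and 15%, about 9%.

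**The case against.** The strongest reply is that an unadjusted rank-sum test is valid under randomisation and conventional, and that the endpoint is secondary in a pilot with no power target. A SAP that is not shown may add adjustment. The validity point stands: nothing here biases the test or inflates type I error. The SAP point stands only in part, because the protocol positively names the test and confines its covariates to survival.

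The case mix is also uncertain. The third inclusion criterion can be read as requiring severe disease, life-threatening disease and CRS together, which might make the sample more uniform. Even so, CRS is itself on the life-threatening list and is defined by laboratory values. If one listed item is enough, a non-ventilated patient can still qualify. The documents allow a mixture but do not establish its size.

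A reader might go further on three points, and the documents do not support these readings:

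- **Pre-randomisation ventilator days are counted.** The endpoint gives no starting point. That is silence, not a statement that such days count.
- **A roughly one-in-four imbalance goes uncorrected everywhere.** That figure assumes that P/F stratification does nothing. The survival models already contain P/F ratio, APACHE II and SOFA.
- **The survival models are deficient without a ventilation term.** Adding one is a reasonable option, but nothing in the protocol makes its absence an error.

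**Conclusion.** The point holds as an efficiency improvement. The stated comparison ignores a recorded entry state that is likely to be strongly related to the endpoint. Using it cost no material power in any setting tried and usually gained some.

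A reader might infer that a large share of the power is thrown away. The documents do not support that. The gains of 15 to 19 points come from assumed inputs with no deaths, whereas the protocol expects half the patients to die. With deaths ranked worst the gain is about 4 to 9 points for 30% to 70% ventilated at entry, and about 2 points at 90%. Power stays below 40% under either test, so stratifying does not rescue the endpoint.

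The larger weakness of this endpoint is separate. With 50% expected mortality and no rule for deaths, an early death can shorten ventilator days and look favourable. Stratifying by entry state does not cure that.

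**What to change.** In the Protocol, Secondary endpoints and Statistical analysis:

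1. State that ventilator days are counted from randomisation in both arms.
2. Compare arms with a rank-sum test stratified by invasive ventilation at randomisation, yes or no (van Elteren).
3. Fix that state at randomisation. Data collection ties Day 0 to the first TPE session, which controls do not have.
4. Give the endpoint its own rule for deaths; the stratified test does not supply one.

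Optionally, add the same yes/no term to the Cox and logistic survival models. That makes nine terms instead of eight (treatment plus the seven listed covariates) for about 60 expected deaths (50% of 120).

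The cost is wording only. Respiratory support is already collected; the one care needed is that the state be recorded as of randomisation.

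### The protocol disclaims allocation concealment because treatment is open label, though its web randomisation can conceal each assignment and its listed mitigations do not address selection bias

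*Protocol*

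**What the plan says.** The relevant text is the Randomization paragraph of the protocol, printed under Secondary endpoints.

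- Order of steps: "Eligible consented patients will be randomized after their stratification by ICU center and two PaO2/FIO2 ratio categories".
- System: "We will utilize a web-based randomization service".
- Blocks: "Randomization will occur in variable block sizes of 4 to 8 patients".
- Concealment: "the intervention will be unblinded (open label); hence, no enrollment concealment will be expedited". The next sentence adds that "the lack of allocation concealment will be mitigated as much as possible by the following measures".
- Measures then offered: "First, the primary outcome of mortality will not be disputable"; "Second, we have standardized co-interventions that impact on mortality as much as possible", with a list a) to e); and, at the end of the paragraph, "We will define the date/time of appropriateness for ICU transfer irrespective of treatment allocation".

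Three other places describe consent. Timeline and Study design say that control patients agree only to the sharing of their data. Consent for TPE says that eligible patients who have consented go on to receive TPE, and does not mention randomisation.

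**The concern.** Concealment means that nobody enrolling a patient knows the next assignment before that patient is irrevocably in the trial. Blinding means that the arm is not known afterwards. TPE cannot readily be blinded, but that does not lead to giving up concealment, so the inference in the protocol is false. The term allocation concealment is used explicitly, so the text cannot simply be read as a remark about blinding. Allocation is also a matter of trial conduct, which an analysis plan cannot repair later.

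If assignments could be foreseen, staff could time or withhold consent to suit the arm. The protocol makes that plausible. Therapeutic options for COVID-19 says TPE is already given empirically, Methodology describes a convenience sample, and Expected Outcome anticipates benefit in at least 60% of patients. The arms could then differ in prognosis at entry, and every death would still be counted correctly. Mortality is a primary endpoint, and the pilot's mortality estimate is meant to inform the sample size of a definitive trial.

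**Working it through.** The protocol gives no figure on this point, so there is none to reproduce. The check has three steps.

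**1. What each listed measure can do**

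| Measure | When it acts | Bias addressed | Limits who enters which arm? |
|---|---|---|---|
| Death as an indisputable outcome | Outcome assessment | Detection | No |
| Standardised co-interventions, a) to e) | After allocation | Performance | No |
| ICU-transfer readiness defined without regard to arm | After allocation | Performance and detection, for ICU stay | No |

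**2. Whether the described process is compatible with concealment**

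It is. Eligibility and consent come first, then the stratum, then the web service assigns the arm. Such a service can release the arm only after registration. Two things weaken this: the explicit disclaimer, and the consent descriptions. A consent limited to data sharing for controls, and a consent followed directly by TPE for the others, suggest that the arm may be known when consent is sought.

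**3. Illustration of what is at stake**

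Inputs from the protocol:
- mortality 50% (Study design, with no time point given);
- about 60 patients per group (Study design);
- two-sided 0.05 (Statistical analysis).

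Assumed: no treatment effect, and a selection-induced difference D in expected mortality between arms. The protocol gives no value for D, so a range is shown.

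For the crude two-proportion test:
- p1 = 0.5 + D/2 and p2 = 0.5 − D/2
- SE0 = √(2 × 0.5 × 0.5 / 60) = 0.0913, so the rejection threshold is 1.96 × 0.0913 = 0.1789
- SE1 = √([p1(1 − p1) + p2(1 − p2)] / 60)
- rejection rate = 1 − Φ((0.1789 − D)/SE1) + Φ((−0.1789 − D)/SE1)

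For D = 0.10: SE1 = √((0.2475 + 0.2475)/60) = 0.0908. The upper tail is 1 − Φ(0.869) = 0.1925 and the lower tail is Φ(−3.07) = 0.0011, together 0.194.

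| Assumed D (points) | False-positive rate |
|---|---|
| 0 | 5.0% |
| 5 | 8.5% |
| 10 | 19.4% |
| 15 | 37.4% |
| 20 | 59.3% |

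To give D a meaning: a net exchange of k patients per arm whose risks differ by r gives D = 2kr/60 = kr/30. With k = 6, D of 5, 10 or 15 points requires r = 0.25, 0.50 or 0.75. Both k and r are assumptions.

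**The case against.** The strongest reply is that the authors wrote concealment where they meant blinding. The sentence starts from the open-label design, the measures that follow are those usually offered for missing blinding, and the order of consent and randomisation is sound. This stands in part: concealment may exist in practice. It does not rescue the text, which names allocation concealment as lacking and gives sites no reason to protect it.

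A reader might infer that assignments are fully predictable. No section describes a list open to sites, so the protocol does not support that.

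A reader might also cite the chance of guessing the next arm within a block. If past assignments in the stratum and the block size are known, the expected proportion of correct guesses is 2.833/4 = 71%, 4.1/6 = 68% and 5.33/8 = 67% for blocks of 4, 6 and 8, against 50% by chance. The arithmetic is right, but the protocol specifies variable sizes, and the same rates would arise in any open-label blocked trial with perfect web concealment. They do not measure the harm of this sentence.

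Nor does the protocol support one figure for the bias. Exchanging 6 of 60 patients per arm between risks of 80% and 20% gives 2 × 6 × 0.6/60 = 12 points, but none of those three inputs is in the document.

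Stratification by P/F category and the planned adjustment for age, gender, P/F ratio, APACHE II, SOFA, coagulopathy and CRS group would absorb part of a measured imbalance. They leave unmeasured selection untouched, do not protect the crude chi-square and log-rank tests, and are not offered as mitigation for missing concealment. The pilot purpose lowers the stakes but does not remove them, because mortality is still compared between arms.

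**Conclusion.** The point holds as an error in the stated rule. The protocol disclaims concealment for a reason that does not justify it, has already chosen a system that can provide it, and offers measures aimed at other biases. It is not shown that assignments will be exposed; the described sequence may conceal them.

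The possible effect on the mortality comparison cannot be sized from the document. The false-positive rates of about 8.5%, 19% and 37% at imbalances of 5, 10 and 15 points are illustrations. They rest on an assumed imbalance, no true effect, the protocol's 50% mortality applied at the time of analysis, 60 patients per arm, and an unadjusted test. With concealment maintained, selection adds no such imbalance and the nominal 5% stands.

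The text should be corrected, because selection at enrolment cannot be undone afterwards and the correction is nearly free.

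**What to change.** 1. Replace the disclaimer with: *Allocation is concealed: the web service reveals the arm only after eligibility, consent and stratum are entered and the patient is irrevocably registered, and block sizes are not disclosed to sites.*
2. Move the block sizes out of the site-facing protocol into a restricted randomisation document. Printing them where sites can read them would contradict the new sentence.
3. Delete the sentence on lacking concealment, and present the listed measures as mitigation for the lack of blinding.
4. Reconcile the consent wording in Timeline, Consent for TPE and Study design, so that every patient (or next of kin) gives the same consent to randomisation before the arm is known. Changing the Randomization paragraph alone would leave this gap open.

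The cost is a protocol amendment, a setting in the service already chosen, and a revision of the consent documents with the ethics review that this requires. Sample size, assessments and patient care do not change.
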